## Methods/Design

The DiaFu study is designed as a national, multicenter, randomized controlled clinical superiority trial across Germany, with blinded photographic analysis of the primary endpoint. Participants are randomly allocated in a 1:1 ratio to each treatment group. Allocation to treatment groups is performed using a centralized web-based tool. To ensure good balance of participant characteristics in each group a stratified randomization is performed. Participants are stratified by study centre and by Wagner-Armstrong stage within each centre (<Wagner-Armstrong stage 2C and ≥ Wagner-Armstrong stage 2C; Figure 1). Due to the physical differences between the treatment regimens it is not possible to blind either participant or physician to the treatment arm. To address issues of blinding, confirmation of wound closure will be assessed via blinded assessment of wound photographs by independent observers.

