### Primary and secondary endpoints

Time until complete (100% epithelization) wound closure and the number of wound closures in each treatment group achieved in the maximum study treatment time of 16 weeks (112 days) are the primary endpoints of the DiaFu study. Complete wound closure is defined by 100% epithelialization of the wound (no granulation tissue visible), no drainage, no sewing material and no need for wound dressing or adjuvants. The assessment of complete wound closure is primarily based on the central blinded review of photographs performed by independent analyzers. Complete wound closure can be achieved either by surgery or by secondary intention. However, surgical intervention (for example wound suture, skin grafting or flap transplantation) is allowed only if the wound bed is prepared adequately. Sustainment of complete wound closure has to be proven by a satisfactory follow-up examination of the area 14 days after the intervention (wound closure verification visit). If the wound cannot be closed before the end of the maximum treatment time of 16 weeks, a study visit to assess the wound status and for evaluation of the secondary endpoints is performed.

Secondary clinical endpoints are the time until complete wound closure within the study time of six months, the number of wound closures per treatment group achieved within six months, the time until optimal preparation of the wound bed for further treatment (a minimum of 95% granulation), recurrences, amputations with incidence and extent, the wound size over time (area of wound opening, maximal length and width (cm^2^)) and the composition of wound tissue (percentage of epithelial layer, granulation tissue and fibrin).

The incidence of serious adverse events (SAEs) including mortality of any cause within six months from the time of initiation of therapy, incidence of device-related adverse events (ADEs) and incidence of wound-related adverse events (AEs) occurring within the study treatment time of 16 weeks or until wound closure confirmation are considered to be safety endpoints of this trial.

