Furthermore, patient reported outcomes (PRO) will be evaluated. Quality of life (QoL) is measured using the questionnaire EQ5D. The questionnaire will be completed by the participant at inclusion, end of the maximum treatment time or end of the therapy and at the six-month follow-up visit . Furthermore, during study visits participants will be asked to provide their assessments of pain with a numerical rating scale (0 to 10). Participants will be asked to provide an estimate of their wound-associated pain of the last 24 hours at each trial visit.

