### Statistical analysis

The analysis of the primary and secondary endpoints will be performed according to the intention-to-treat principle (ITT). There will be no interim analysis. The ITT analysis population will include all randomized participants who have a valid baseline and at least one valid post baseline wound assessment (examination). For the ITT analysis population, participants will be assigned to the treatment group based on the randomization schedule, regardless of the treatment actually received. As a secondary approach a per protocol (PP) analysis will be performed excluding patients with any serious protocol deviations and changes of wound treatment. The rates of wound closure will be compared using Fisher’s exact test and time to complete closure will be compared using the Log-rank test. Safety data will be presented on an ‘as treated’ basis where patients will be grouped according to the exact wound treatment performed. Safety and secondary endpoints will be analyzed using conventional univariate testing. For the analysis of the primary efficacy endpoint missing values will be incorporated as censored values.

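### Univariate testing for secondary outcomes that also have a baseline value (wound size, tissue composition, pain, EQ5D) gives away precision that baseline adjustment would recover

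*Protocol article*

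**What the plan says.** The Statistical analysis section gives one rule for everything beyond the two primary endpoints: "Safety and secondary endpoints will be analyzed using conventional univariate testing". It names no test, time point or scale, but it does settle the class of method.

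Several outcomes under that rule are repeated measurements. The Primary and secondary endpoints section lists "the wound size over time (area of wound opening, maximal length and width", together with the percentages of epithelial, granulation and fibrin tissue. On pain it says: "Participants will be asked to provide an estimate of their wound-associated pain of the last 24 hours at each trial visit". On EQ5D it says: "The questionnaire will be completed by the participant at inclusion, end of the maximum treatment time or end of the therapy", with a further completion at the six-month follow-up visit.

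A starting value for the wound is built into the analysis population, which requires "a valid baseline and at least one valid post baseline wound assessment". The Methods/Design section says of the randomisation: "Participants are stratified by study centre and by Wagner-Armstrong stage within each centre". The article describes no adjustment for baseline or stratum for any secondary endpoint.

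**The concern.** A univariate two-group comparison has no term for the patient's starting value and none for the stratification factors. How large a wound is at the start is likely to say something about how large it is later, and the same goes for pain and quality of life. An analysis without that information leaves explainable variation in the error term.

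At stake is the width of the confidence intervals, and the chance of detecting a real difference, for the outcomes that describe the wound and the patient's experience. Patient-reported outcomes also serve as an effectiveness measure in the cost-effectiveness analysis. The sensitivity analysis there uses the bounds of the 95% intervals, so an interval wider than the data require could carry over into the economic result.

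**Working it through.** **Inputs from the protocol article**
- Planned size: 162 per group, 324 in total (Power calculation).
- Assumed closure rates: 45% and 30%; α = 0.05; power 80% (Power calculation). Sidedness is not stated and is taken as two-sided.
- Allocation 1:1 (Methods/Design).

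**Assumptions, not in the article**
- Correlation r between baseline and follow-up: 0.3, 0.5 and 0.7.
- Equal standard deviations at both times (needed for the change-score formula), a linear relation, and complete data.
- An illustrative true difference of 0.25 SD for the power figures.

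**Step 1: the plan's own figure.** No calculation is given for any secondary endpoint, so the only figure to reproduce is the primary sample size, which supplies n per arm. With the pooled normal approximation:

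n = [1.96·√(2·0.375·0.625) + 0.842·√(0.45·0.55 + 0.30·0.70)]² / 0.15² ≈ 162.3, rounded up to 163.

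The plan has 162, at which power is 79.9%. The figure reproduces.

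**Step 2: relative variance of the treatment contrast.** Take a test on follow-up values as 1. Then:
- change from baseline: 2(1 − r)
- baseline-adjusted (ANCOVA): 1 − r²
- ANCOVA relative to change: (1 − r²) / [2(1 − r)] = (1 + r)/2

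| r | Follow-up only | Change score | ANCOVA | ANCOVA ÷ change |
|---|---|---|---|---|
| 0.3 | 1.00 | 1.40 | 0.91 | 0.65 |
| 0.5 | 1.00 | 1.00 | 0.75 | 0.75 |
| 0.7 | 1.00 | 0.60 | 0.51 | 0.85 |

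ANCOVA beats the follow-up test at any r above 0 and the change-score test at any r below 1. Below r = 0.5 a change score is worse than plain follow-up values.

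**Step 3: in patients.** The precision of 162 per arm with a follow-up-only test is reached by ANCOVA with 162 × (1 − r²) ≈ 147, 122 and 83 per arm at r = 0.3, 0.5 and 0.7. Put the other way, the extra patients needed for equal precision are:
- follow-up-only test, 1/(1 − r²) − 1: 10%, 33% and 96%
- change-score test, 2/(1 + r) − 1: 54%, 33% and 18%

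**Step 4: detectable difference and power at 162 per arm.** With V the relative variance, the difference detectable at 80% power is (1.96 + 0.842)·√(2V/162). Power at 0.25 SD is Φ(0.25·√(162/(2V)) − 1.96).

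| Analysis | V | Detectable difference (SD) | Power at 0.25 SD |
|---|---|---|---|
| Follow-up only | 1.00 | 0.311 | 61% |
| ANCOVA, r = 0.3 | 0.91 | 0.297 | 66% |
| ANCOVA, r = 0.5 | 0.75 | 0.270 | 74% |
| ANCOVA, r = 0.7 | 0.51 | 0.222 | 88% |

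**The case against.** The strongest reply is that the sentence names a class of tests, not a test, in an article that condenses a fuller protocol. A reader might infer that wound size will be compared visit by visit, with the baseline ignored, many separate p-values, and anyone who missed a visit dropped. The article says none of this. A univariate test can be run on change from baseline or on a per-patient summary such as a slope or area under the curve, and these use the baseline, the repeated visits or both. That part of the reply stands. What survives is narrower: even the change score, which does use the baseline, is less precise than adjusting for it. An analysis plan that adjusted for covariates would depart from the published sentence rather than fill it in.

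A reader might also infer bias from chance imbalance in starting wound size. The design does not support that. The article states: "Participants are randomly allocated in a 1:1 ratio to each treatment group". With complete data, an unadjusted test after randomisation is valid, its type I error already allows for chance imbalance, and ignoring the strata tends to make it conservative.

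Three further limits stand:
- The gain depends on an r that nobody can read from the article; at r = 0.3 the variance reduction against a follow-up test is only 9%.
- With 30% to 45% of wounds expected to close by week 16, follow-up area will have many zeros. The linear formulas are then only a rough guide for that outcome, and a Gaussian mixed model would suit it poorly.
- The required baseline is a wound assessment. It does not guarantee baseline pain or EQ5D for everyone, and the first EQ5D follow-up falls at the end of maximum treatment or of therapy, so a uniform week-16 contrast would not fit it.

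**Conclusion.** The point holds as a loss of efficiency for the continuous outcomes measured at baseline and again later: wound size, tissue composition, pain and EQ5D. Over an assumed r of 0.3 to 0.7, baseline adjustment would lower the variance of the treatment contrast by 9% to 49% against a follow-up-only test and by 15% to 35% against a change-score test. These figures rest on the assumed r, a linear relation, complete data and, for change scores, equal standard deviations. They are least secure for wound area.

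It is not a finding of bias or inflated error. It does not touch the two primary endpoints or the sample size, and it does not extend to recurrences, amputations, closure counts or times to an event, which have no baseline value of the same outcome. It is a modest but worthwhile improvement.

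**What to change.** Restrict the existing sentence to safety and single-occasion outcomes such as recurrences, amputations and closure counts. For wound size, tissue composition, pain and EQ5D, prespecify the following:

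- **Adjustment:** the baseline value of the outcome and the Wagner-Armstrong stratum (below 2C, or 2C and above), with centre included, for example as a random effect.
- **Model:** ANCOVA at a named time point that fits the outcome's own schedule, or a repeated-measures model where there are several visits. For EQ5D the time points are the end-of-treatment and six-month completions.
- **Wound area:** a scale, or a rank-based or robust method, that handles the many zeros after closure.
- **Reporting:** the adjusted difference with its 95% confidence interval.

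The change needs no additional measurements or patients: the baseline measurements are already scheduled and the stratification factors are known from randomisation. It costs a few sentences of analysis text, a little more programming, and checks of the model assumptions.

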### Power calculation

The superiority hypothesis is tested in parallel with two different outcomes for the rate of wound closure and the time to wound closure in a fixed maximum treatment period of 16 weeks. The method of Bonferroni-Holm will be used for the adjustment of the α-error for parallel confirmatory testing of both primary endpoints. This means that after testing for both endpoints the smaller P value has to be <0.025 while the other has to be <0.05 for statistical significance. The sample size calculation is based primarily on the difference between wound closure rates in both treatment arms. The expected difference of the wound closure rates is based on information extracted from published previous studies. Armstrong and Lavery [16] described a rate of complete wound closure within 56% of patients with NPWT and within 39% of patients in the corresponding control group. Blume [17] showed a rate of complete wound closure within 43% of patients treated with NPWT and 29% of patients in the control group. For the present study success rates for achieving of the primary endpoint of 45% for NPWT and 30% in the control group are assumed, resulting in an absolute difference of at least 15% in the rate of complete wound closure results. Based on a type one error of α = 0.05 and a type two error of β = 0.2 (corresponding to a power of 80%) a total sample size of 162 patients per group (324 in total) is needed to prove the primary endpoint (wound closure rate).

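### The single missing-data rule, censoring, does not fit the closure rate tested by Fisher's exact test, and for time to closure it leaves open how failure-related stops are handled

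*Protocol article*

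**What the plan says.** Protocol article, Primary and secondary endpoints, names two primary endpoints: "Time until complete (100% epithelization) wound closure and the number of wound closures in each treatment group achieved in the maximum study treatment time". That limit is set at 16 weeks. Statistical analysis assigns the tests: "The rates of wound closure will be compared using Fisher’s exact test and time to complete closure will be compared using the Log-rank test". Power calculation makes both confirmatory: "The method of Bonferroni-Holm will be used for the adjustment of the α-error for parallel confirmatory testing of both primary endpoints". The smaller p-value must be below 0.025 and the other below 0.05. The sample size rests on the closure rate.

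The only missing-data rule for these endpoints is in Statistical analysis: "For the analysis of the primary efficacy endpoint missing values will be incorporated as censored values". The word endpoint is singular there. The article does not say which of the two is meant, what counts as missing, or at what time a patient is censored. The ITT set requires only a valid baseline and one later wound assessment, so it can contain patients whose status at day 112 is unknown.

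Among the secondary endpoints are "recurrences, amputations with incidence and extent". Death is counted as a safety endpoint. Neither is given a role in the primary analysis. Table 2, under Avoiding potential bias, lists evaluation on the number of patients randomized as a criterion, and the article says the trial is designed to avoid all potential bias.

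**The concern.** Censoring belongs to time-to-event analysis. Fisher's exact test needs each patient classed as closed or not closed, so for the closure rate the rule gives no instruction that can be carried out. An analyst must choose between leaving the censored patients out and counting them as not closed. Leaving them out compares completers only and conflicts with the Table 2 criterion.

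For the log-rank test the rule can be carried out, but it rests on an assumption. A patient censored at the last assessment is taken to have had the same later chance of closure as those still observed. That is implausible for a patient who died or withdrew because the wound was getting worse, and for one with an amputation if that ended wound assessment.

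The trial is unblinded for patients and physicians, so losses could differ between arms. If they do, both confirmatory results would depend on a choice that the plan does not make.

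**Working it through.** **Inputs from the article.** Power calculation: "success rates for achieving of the primary endpoint of 45% for NPWT and 30% in the control group are assumed"; "Based on a type one error of α = 0.05 and a type two error of β = 0.2"; 162 patients per group.

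**Stated sample size.** Two proportions, two-sided 0.05, 80% power, pooled variance under the null (mean rate 0.375), no continuity correction:

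n = [1.960·√(2·0.375·0.625) + 0.842·√(0.45·0.55 + 0.30·0.70)]² / 0.15² ≈ 162.3.

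This is 162, or 163 rounded up. The stated figure reproduces and the point does not turn on it. The article states no allowance for drop-out.

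**Closure rate.** Expected closures are 0.45·162 ≈ 73 and 0.30·162 ≈ 49. The losses are assumptions, and every lost patient is taken to be a non-closer.

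| Handling | NPWT | Control | Difference (points) | Fisher p |
|---|---|---|---|---|
| All patients kept, lost = not closed | 73/162 = 45.1% | 49/162 = 30.2% | 14.8 | 0.008 |
| 8 NPWT and 24 control left out | 73/154 = 47.4% | 49/138 = 35.5% | 11.9 | 0.044 |
| 24 NPWT and 8 control left out | 73/138 = 52.9% | 49/154 = 31.8% | 21.1 | 0.0003 |
| 16 left out per arm | 73/146 = 50.0% | 49/146 = 33.6% | 16.4 | 0.006 |

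The number of closures is the same in every row; only the denominators move. With wider assumed losses (5% of NPWT and 20% of control, and the reverse) the difference runs from 9.7 to 24.3 points.

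**Time to closure.** Simulation with 162 per arm. Assumptions: closure times uniform over days 14–112; patients who stop early are all non-closers; stopping times spread over the treatment period; log-rank test at two-sided 0.05. Censoring at the stopping time is compared with keeping the patient at risk as not closed to day 112.

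- True rates 45% v 30%, stops 5% NPWT and 15% control: power is about 65% with censoring and about 79% when kept at risk.
- The same with the stops reversed: about 92% with censoring.
- No true difference (30% in both arms), stops 5% NPWT and 15% control: two-sided type I error is about 6–7% with censoring, and most false rejections favour control.
- No true difference, more stops under NPWT: false rejections in favour of NPWT are 6.1% (20% v 10%) or 13.2% (30% v 10%), against a nominal 2.5%. Keeping the patients at risk gives 2.8–2.9%.
- Equal stops of 10% in both arms: two-sided type I error is 4.3% with censoring and 4.4% when kept at risk; power is 81% and 79%.

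**The case against.** The strongest reply is that the rule, with its singular endpoint and its survival-analysis term, is meant for time to closure only, and that the closure rate is already settled by context. The analysis is by ITT, the endpoint counts closures, and a closure must be reached by day 112 and confirmed for 14 days, so an undocumented closure is no closure. A full analysis plan may also say more. Part of this stands: a reader might infer that the plan prescribes a completers-only Fisher test and therefore inflates the closure rate, but no sentence says that patients leave the table. What remains is that, on this reading, the article states no missing-data rule for the endpoint on which the trial is sized.

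Three other stronger readings also go beyond the text.

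- **Amputation as a missing value.** The article does not call it one. Setting lists amputation as a form of wound preparation and Participants admits amputation wounds, so such a patient may stay under observation. Death is different: no later assessment exists, so censoring is the natural result of the only rule given.
- **Censoring at the last assessment.** This is the ordinary reading, but it is not stated. Censoring non-closers at day 112 would largely remove the log-rank problem.
- **Failure under Bonferroni-Holm.** A reader might take p = 0.044 as a failed test. Under the article's own rule it still counts if the log-rank p-value is below 0.025.

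It is also fair to object that the unequal losses are assumed. No figure in the article supports a threefold imbalance, and with balanced losses little changes.

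**Conclusion.** The concern holds in this limited form. A stated rule cannot be applied to one of two confirmatory endpoints, or else leaves that endpoint uncovered; either way the sentence has to change. This part needs no assumption about losses. Its effect on the result does: 11.9 to 21.1 points instead of 14.8 if non-closers lost in an 8-to-24 split are left out, and 16.4 points if 16 are lost from each arm.

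For time to closure the concern is conditional on censoring at the last assessment and on failure-related losses that differ by arm. Under the assumed 5% and 15%, the effect on power is large (about 79% to 65% or 92%) and the effect on type I error is modest (about 6–7% instead of 5%). With equal losses the type I error is near nominal. The exact power figures also depend on the assumed closure-time distribution, which the article does not give.

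**What to change.** Replace the single sentence with one rule per endpoint, fixed before the analysis.

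- **Closure rate.** Keep all randomized patients in the denominator. Any patient without documented closure by day 112, confirmed as the endpoint definition requires, counts as not closed. This also meets the number-randomized criterion in Table 2.
- **Time to closure.** State the censoring time. Patients who die, lose the study wound to amputation or withdraw for a worsening wound stay at risk as not closed to day 112, which handles these as competing events. Only other losses are censored at the last wound assessment. Withdrawal for a worsening wound belongs in the first group; censoring it would leave the informative losses in the primary test.
- **Sensitivity.** Add a tipping-point or multiple-imputation analysis for the other losses.

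The cost is a few sentences and one extra analysis. Closure rates become somewhat conservative, because a patient who healed without documentation counts as not closed.

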### Power calculation

The superiority hypothesis is tested in parallel with two different outcomes for the rate of wound closure and the time to wound closure in a fixed maximum treatment period of 16 weeks. The method of Bonferroni-Holm will be used for the adjustment of the α-error for parallel confirmatory testing of both primary endpoints. This means that after testing for both endpoints the smaller P value has to be <0.025 while the other has to be <0.05 for statistical significance. The sample size calculation is based primarily on the difference between wound closure rates in both treatment arms. The expected difference of the wound closure rates is based on information extracted from published previous studies. Armstrong and Lavery [16] described a rate of complete wound closure within 56% of patients with NPWT and within 39% of patients in the corresponding control group. Blume [17] showed a rate of complete wound closure within 43% of patients treated with NPWT and 29% of patients in the control group. For the present study success rates for achieving of the primary endpoint of 45% for NPWT and 30% in the control group are assumed, resulting in an absolute difference of at least 15% in the rate of complete wound closure results. Based on a type one error of α = 0.05 and a type two error of β = 0.2 (corresponding to a power of 80%) a total sample size of 162 patients per group (324 in total) is needed to prove the primary endpoint (wound closure rate).

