
### Aim of the DiaFu study

This RCT is designed to prove that NPWT therapy leads more frequent and earlier to complete healing of diabetic foot wounds as compared to conventional moist wound therapy. Furthermore, it aims to show that NPWT therapy is also safe and effective when provided in an ambulatory care setting and to prove its overall cost-effectiveness. This trial is designed to comply with all quality requirements (randomized trial, low potential for bias; see Discussion section) of IQWiG and G-BA, as well as other European authorities.

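### The plan names Bonferroni-Holm but explains it as a requirement on both p-values, which would discard a valid rejection of one endpoint

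*Protocol article*

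**What the plan says.** Under Power calculation, the article sets up the confirmatory test in three steps.

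- The hypothesis is in the singular, with two outcomes: "The superiority hypothesis is tested in parallel with two different outcomes for the rate of wound closure and the time to wound closure".
- The multiplicity method is named: "The method of Bonferroni-Holm will be used for the adjustment of the α-error for parallel confirmatory testing of both primary endpoints".
- The next sentence says what this means in practice: "the smaller P value has to be <0.025 while the other has to be <0.05 for statistical significance".

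Statistical analysis assigns Fisher's exact test to the closure rate and the log-rank test to time to closure. Primary and secondary endpoints lists both as primary, within 16 weeks (112 days). Aim of the DiaFu study says the trial is to prove that "NPWT therapy leads more frequent and earlier to complete healing of diabetic foot wounds". None of these sections says whether success on one endpoint makes the trial positive.

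**The concern.** Holm is a step-down procedure that gives a separate verdict for each endpoint. With two endpoints, the smaller p-value is compared with 0.025. If it passes, that endpoint is significant and the verdict is final. Only then is the larger p-value compared with 0.05, and its failure does not undo the first rejection.

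The article's sentence has the right two thresholds but joins them into one condition for significance. It leaves out that the first step is sufficient for its own endpoint. Anyone who applies the sentence as printed would report no significant result where Holm gives a valid claim on one endpoint. Because the number of endpoints needed is not stated either, the choice between the two readings could be made after the p-values are known. The article says the results will feed a national reimbursement decision, so the rule should have only one reading.

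**Working it through.** **Inputs from the article.** Closure rates: "success rates for achieving of the primary endpoint of 45% for NPWT and 30% in the control group are assumed". Error rates: "Based on a type one error of α = 0.05 and a type two error of β = 0.2". Group size: 162 per group with 1:1 allocation. Tests: Fisher's exact and log-rank, with follow-up to day 112. Sidedness is not stated.

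**Reproducing the plan's own figure.** For 45% versus 30%, two-sided α = 0.05 and 80% power:

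- Pooled normal approximation: n = [1.960·√(2·0.375·0.625) + 0.842·√(0.45·0.55 + 0.30·0.70)]² / 0.15² = 162.3 per group.
- Arcsine: h = 2·asin(√0.45) − 2·asin(√0.30) = 0.311, and n = 2·(1.960 + 0.842)² / h² = 161.9, so 162.

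One-sided 0.05 would give 128. The stated 162 is therefore right for its own inputs with a two-sided test, and two-sided tests are used below.

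**The two rules side by side.** Let p(1) be the smaller and p(2) the larger p-value.

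| Result | Holm | Sentence as printed |
|---|---|---|
| p(1) < 0.025 and p(2) < 0.05 | both endpoints significant | significant |
| p(1) < 0.025 and p(2) ≥ 0.05 | endpoint with p(1) significant | nothing significant |
| p(1) ≥ 0.025 | nothing significant | nothing significant |

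They differ only in the middle row. For example, 66/162 versus 49/162 closures gives Fisher p = 0.063. If the log-rank p-value lay just under 0.025 (an illustrative assumption), Holm would declare time to closure significant and the printed sentence would declare nothing.

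**How often the middle row occurs.** Simulation of 20,000 trials per scenario, 162 per arm, 45% versus 30% closed by day 112, no drop-out, censoring at day 112. The closure-time distributions are assumptions, since the article gives none.

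| Timing of closures | Holm, at least one endpoint | Printed joint rule | Difference |
|---|---|---|---|
| Constant hazards | 72.9% | 72.5% | 0.4 points |
| NPWT earlier (Weibull shape 1 NPWT, 2 control) | 84.6% | 76.4% | 8.2 points |
| Reverse timing | 67.8% | 65.3% | 2.5 points |

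The printed rule is nested inside Holm, so each difference is also the share of trials with a different verdict. Further runs of 10,000 trials gave 0.5% for constant hazards and 7.7% to 8.0% for earlier NPWT closures.

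**Under the null** (30% in both arms, constant hazards, 10,000 trials): at least one Holm rejection in 2.59%, printed rule satisfied in 2.55%.

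**The case against.** The strongest reply is that the named method governs. Bonferroni-Holm is fully defined, both thresholds are correct, and the sentence can be read as shorthand in which each p-value is held to its own limit for its own significance. The article also condenses a fuller protocol. This reading is possible, but the text does not force it. The sentence is offered as the meaning of the method, its grammar is conjunctive, and no other section corrects it. The point therefore concerns a rule that the article states, not a detail left to another document.

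It is also fair to say that the literal reading is stricter than Holm and cannot create a false claim, and that the larger gap needs an assumed timing pattern. Both stand, and they limit the weight of the point.

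A reader might infer more than the document supports:

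- **A third rule, closure rate alone.** The sample size rests on the closure rate, but sizing on one of two primary endpoints does not define success. The article names both as primary and tests both.
- **A both-endpoints rule with each test at 0.05.** The article states no such rule. The joint wording of the aim is a general statement of purpose and is not a formal hypothesis.
- **A loss of α specific to the printed sentence.** The null rejection rate is well below 0.05, but it is practically the same under correct Holm. It comes from the 0.025 first step with highly correlated tests and from the conservatism of Fisher's test.
- **Strongly conflicting p-values as a typical result.** A log-rank p ≤ 0.01 with a Fisher p ≥ 0.08 did not occur in 10,000 trials with constant hazards, and occurred in no more than 0.13% under the early-closure assumption.

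**Conclusion.** The concern holds in a limited form. The explanatory sentence does not describe the method it claims to explain. Taken literally, it removes a rejection that Holm allows, and the article does not say whether one endpoint is enough.

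The loss is about 0.5% of trials if hazards are constant, and about 8% if NPWT closures come earlier at unchanged day-112 rates. Both figures assume the plan's 45% versus 30%, 162 per group, no drop-out and two-sided tests. The 8% also depends on the assumed Weibull shapes. Type I error is not inflated, and the sample size is correct for its stated inputs. Severity is low, but the text is wrong as written and easy to correct.

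**What to change.** Under Power calculation, replace the explanatory sentence with: *The endpoint with the smaller two-sided p-value is significant if p < 0.025; only then is the other tested, and it is significant if p < 0.05. Superiority is concluded for each endpoint so rejected.* Add a statement that one rejected endpoint suffices for a positive trial.

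The cost is a few lines of text, fixed before database lock, with no additional patients, data or analyses. The sponsor has to commit in advance to the either-endpoint criterion and to report which endpoint was rejected.
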